
**Fig. 1 Fig1:**
[figure not shown]
Flow diagram of the study procedure

### Study outcomes

In the present study, we have multiple primary outcomes due to the nature of the dietary interventions as seen in many other randomized clinical trials [18, 19]. A single outcome may be insufficient to fully describe the effects of an intervention on a complex disease, namely metabolic syndrome. Weight, body composition, and CTRP6 (as an inflammatory marker) are the main primary outcomes in the current study. Sample size calculation has been estimated on the body weight changes as the largest number achieved in each group. Hence, our primary endpoints will be the mean difference in the changes from baseline to 10-week follow-up in body composition component (weight and body fat mass) and CTRP6 concentration between the intervention groups. Study success will be declared if either one of the primary endpoints will be statistically significant in favor of the experimental treatment.

The main secondary outcomes would be lipid profile, glycemic indices, serum insulin, leptin, and plasma EMPs (CD31+/CD42b− and CD144+/CD42b−). Satiety, hunger, fullness and desire to eat [20], inflammatory factors (chemerin, FGF-21, Asprosin), PYY, ghrelin, and creatinine are exploratory outcomes.

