**Methods:**

Eighty metabolic syndrome patients will be recruited in this study. They will be randomly allocated to one of the following 4 groups: (1) receiving a modified-Paleo diet with calorie counting, (2) receiving a modified-Paleo diet with a fixed diet plan, (3) receiving a medium-carbohydrate diet with calorie counting, and (4) receiving a medium-carbohydrate diet with a fixed diet plan for 10 weeks. Weight, height, waist circumference, and body composition will be assessed at the study baseline and at the end of the trial. Serum insulin, asprosin, chemerin, FGF-21, CTRP-1, PYY, ghrelin, plasma EMPs (CD31+/CD42b− and CD144+/CD42b−), lipid profile, glycemic indices, hs-CRP, leptin, vitamin C, creatinine and satiety, hunger, fullness, and desire to eat (via visual analog scales) will be measured at the study baseline and at the end of the trial. Insulin resistance and insulin sensitivity will be determined using the HOMA-IR and QUICKI equations.

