### Blood sampling, biochemical, and flow cytometric measurements of EMPs

In a 12-h fasting state, a 10-ml venous blood sample will be taken from each participant at the beginning and the end of the study. After centrifuging for 15 min (3000 rpm), the serum samples will be separated and simultaneously stored at − 80 °C until analysis. Serum lipid profiles (TC, HDL, LDL, and TG) and blood glucose levels will be measured by the enzymatic colorimetric method using commercial kits. Serum insulin, asprosin, chemerin, FGF-21, CTRP-1, PYY, and ghrelin will be measured using an enzyme-linked immunosorbent assay (ELISA) kit. Insulin resistance and insulin sensitivity will be measured by the HOMA-IR and QUICKI formulae, respectively.
$$ \mathrm{QUICKI}=1/\left(\log\ \left(\mathrm{fasting}\ \mathrm{insulin}\ \upmu \mathrm{U}/\mathrm{ml}\right)+\log\ \left(\mathrm{fasting}\ \mathrm{glucose}\ \mathrm{mg}/\mathrm{dl}\right)\right) $$$$ \mathrm{HOMA}-\mathrm{IR}=\left(\mathrm{FBI}\ \left(\mathrm{mU}/\mathrm{l}\right)\times \mathrm{FBS}\ \left(\mathrm{mmol}/\mathrm{l}\right)\right)/22.5 $$

Flow cytometric assessment of endothelial-derived microparticles will be performed according to the study of Mikirova et al. [26]. In order to quantify the level of circulating EMPs, 5–10 ml blood will be collected in tubes containing EDTA. The plasma will be processed within 30 min to 1 h after blood collection by two-step centrifugation. Microparticles in the platelet-poor plasma samples will be quantified by flow cytometry as described in previous studies. Briefly, 50 μl of platelet-poor plasma will be incubated with 5 μl of antibodies: anti CD31, CD42b, and CD144, all from Biolegend (San Diego, CA, USA). After staining, the plasma will be diluted by 350 μl of PBS with 10 mmol citrate; 50 μl of 5 μm AccuCount standard beads (Spherotech, Libertyville, IL) will be added to the sample before analysis to allow calculating of MP values. Samples will be analyzed on a flow cytometer (Quanta, Beckman Coulter) with the relevant FlowJo software, and the final data will be expressed as an absolute count of microparticle/μl.

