## Abbreviations

MetS: Metabolic syndrome
NCD: Non-communicable diseases
CVD: Cardiovascular diseases
EMPs: Endothelial microparticles
VAS: Visual analog scales
FGF-21: Fibroblast growth factor 21
CTRP-1: C1q/TNF-α–related protein 1
PYY: Peptide YY
hs-CRP: High-sensitivity C-reactive protein
HOMA-IR: Homeostatic Model Assessment for Insulin Resistance
QUICKI: Quantitative insulin-sensitivity check index
NCEP: National Cholesterol Education Program
ATPIII: Adult Treatment Panel III
NAFLD: Non-alcoholic fatty liver disease
MPs: Microparticles
CONSORT: Consolidated Standards of Reporting Trials
SPIRIT: Standard Protocol Items: Recommendations for Interventional Trials
SAMPL: Statistical Analyses and Methods in the Published Literature
NSAIDs: Non-steroidal anti-inflammatory drugs
HRT: Hormone replacement therapy
WC: Waist circumference
BMI: Body mass index
BIA: Bioelectric impedance analysis
IPAQ: International Physical Activity Questionnaire
TC: Total cholesterol
HDL: High-density lipoprotein
LDL: Low-density lipoprotein
TG: Triglycerides
EDTA: Ethylene diamine tetra acetic acid
CD: Cluster of differentiation
PBS: Phosphate-buffered saline
NHST: Null hypothesis significance testing
ANOVA: Analysis of variance
ANCOVA: Analysis of covariance
TSC: Trial Steering Committee

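### The primary biomarker is named CTRP6 in the outcomes section but only CTRP-1 in the measurement lists, so one of three primary endpoints cannot be identified

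*Protocol article*

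**What the plan says.** All references are to the protocol article.

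- **Study outcomes** names CTRP6 twice. First: "Weight, body composition, and CTRP6 (as an inflammatory marker) are the main primary outcomes in the current study". Then the endpoint definition takes changes from baseline to 10 weeks in "body composition component (weight and body fat mass) and CTRP6 concentration between the intervention groups". This gives three primary endpoints: weight, body fat mass and CTRP6.
- **Study outcomes** also sets the success rule: "Study success will be declared if either one of the primary endpoints will be statistically significant in favor of the experimental treatment".
- **Blood sampling, biochemical, and flow cytometric measurements of EMPs** lists the ELISA analytes: "Serum insulin, asprosin, chemerin, FGF-21, CTRP-1, PYY, and ghrelin will be measured using an enzyme-linked immunosorbent assay (ELISA) kit".
- **Abstract, Methods** gives the longer list of what is measured, which includes "Serum insulin, asprosin, chemerin, FGF-21, CTRP-1, PYY, ghrelin, plasma EMPs" and goes on to hs-CRP, leptin, vitamin C and creatinine, among others. CTRP6 is not in it.
- **Abbreviations** has one CTRP entry: "CTRP-1: C1q/TNF-α–related protein 1".

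**The concern.** The number is part of the protein's name in the article's own abbreviation list, so CTRP6 and CTRP-1 read as two different analytes. One is a primary endpoint with no described measurement. The other is measured but stands in no outcome tier.

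What makes this more than an editorial matter is the success rule. Because any single primary endpoint suffices, the CTRP endpoint can make the trial positive by itself. An analyst holding CTRP-1 data could treat CTRP6 as a misprint and report CTRP-1 as primary. The same analyst could follow the outcomes section literally and report CTRP-1 as an unclassified marker. Both readings can be defended from the text, so the status of the result could be chosen once it is known.

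**Working it through.** The article states no figure on this point, so the check is a cross-reading of every place where a CTRP is named, followed by a match of outcomes to measurements in both directions.

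**Step 1. Every mention of a CTRP.**

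| Section | CTRP6 | CTRP-1 |
|---|---|---|
| Abstract, Methods | no | measured |
| Study outcomes | primary (twice) | no |
| Blood sampling, biochemical, and flow cytometric measurements of EMPs | no | measured by ELISA |
| Abbreviations | no | defined |

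No section names both, and no sentence links them.

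**Step 2. From assay to outcome tier.** The ELISA sentence lists seven analytes.

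| ELISA analyte | Tier in Study outcomes |
|---|---|
| Insulin | secondary |
| Asprosin | exploratory |
| Chemerin | exploratory |
| FGF-21 | exploratory |
| CTRP-1 | none |
| PYY | exploratory |
| Ghrelin | exploratory |

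Six of the seven have a tier. CTRP-1 is the only one without.

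**Step 3. From outcome tier to measurement.** Weight and body fat mass have their own assessment sections. Lipids, glucose, insulin and the microparticles are in the laboratory section, as are chemerin, FGF-21, asprosin, PYY and ghrelin. Appetite ratings are described under Study design. Leptin is in the abstract's measurement list, and creatinine is there and under Intervention safety. CTRP6 is the only outcome with a tier that appears in none of these places.

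**Step 4. Reading the two mismatches together.** There is one orphan on each side, and both are CTRPs. That fits two explanations:

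1. One protein was meant throughout and is misnamed in one place.
2. The analyte was changed and the change reached only Study outcomes, or only the measurement lists.

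The article is version 2 of the protocol, and the text shown does not say which explanation applies.

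**Step 5. What is affected.** One of three primary endpoints. Study outcomes and Sample size both base the calculation on body weight; CTRP does not enter it, so the planned 80 participants do not change.

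**The case against.** The strongest reply is that nothing is actually missing. Outcome measurements says that every outcome measure is assessed at baseline and week 10, which by its terms covers whatever Study outcomes lists. The laboratory section is not exhaustive: leptin, hs-CRP, vitamin C and creatinine have no assay there either. The assessment schedule in Fig. 2 is not shown and might name the protein. The one-for-one mismatch also makes a simple naming slip plausible, and then the endpoint would have data. Nor is CTRP-1 alone in lacking a tier: hs-CRP is also measured and unclassified.

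Much of this stands. A reader might infer that the trial will have no CTRP6 data, or that a primary endpoint is lost. The article does not support that; it supports only that no CTRP6 measurement is described. The reply does not remove the contradiction, however. The general sentence names no analyte or assay. The abstract's list supplies all four analytes missing from the laboratory section and still omits CTRP6. A slip in the identity of a primary endpoint is still an error in that endpoint.

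A reader might also want an error rate: if both proteins were assayed and either could be called primary, four endpoints at 0.05 would give 1 − 0.95^4 = 18.5%, against 1 − 0.95^3 = 14.3% for three. This should not be relied on. The article describes no such double assay, and independence is doubtful because weight and body fat mass move together. Success also requires an effect favouring the experimental treatment. Counting only that direction, at 0.025 per endpoint, gives 1 − 0.975^4 = 9.6% against 1 − 0.975^3 = 7.3%. In either version the figure for three endpoints comes from the any-one success rule, which is a separate question from which protein is meant.

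**Conclusion.** The contradiction is real and must be corrected. Study outcomes conflicts with the abstract, the laboratory section and the abbreviations on which CTRP is the primary biomarker, and nothing in the article reconciles them. The size is one unidentified endpoint out of three, under a rule by which that endpoint alone can declare success. No error-rate figure is needed, and the sample size is not touched.

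The conclusion rests on the text shown. Fig. 2 and the registry entry were not available, and either might show which protein was intended. They would not make the current wording consistent.

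**What to change.** Before any CTRP result is analysed, reconcile the abstract, Study outcomes, the laboratory section and the abbreviations against the dated registry entry or the original protocol. The article says the full protocol is accessible on the registry. That prior record should decide the endpoint, not whichever assay happened to be run. Then name one protein, with its assay, as the primary marker:

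- **If CTRP-1 was prespecified:** correct CTRP6 to CTRP-1 in both places in Study outcomes. It stays primary.
- **If CTRP6 was prespecified:** add it to the abstract, the assay list and the abbreviations, and give CTRP-1 an outcome tier if it is also measured.
- **If the prespecified marker will not be assayed:** remove it from the primary endpoints and the success rule by a dated, documented amendment, and state the tier of any CTRP that is measured.

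The article already provides for amendments to be notified and posted on the registry. In the first and third cases the cost is a text and registry correction. In the second, if CTRP6 is not yet planned, there is also an added assay on serum held at −80 °C, for up to 80 × 2 = 160 samples, provided enough serum remains.

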### Intervention

The participants will be randomly allocated to one of the four aforementioned groups. Accordingly, each participant will be trained in a pre-designed low- or medium-carbohydrate dietetic regimen during a 1-h face-to-face conversation. Everyone will receive a diet plan based on their weight and their daily calorie needs. In the present study, the modified-Paleo diet is defined as 20% carbohydrate, 35% protein, and 45% fat, and the moderate-carbohydrate diet is defined as 40% carbohydrate, 30% protein, and 30% fat. The cooking tips for some of the foods in modified-Paleo menus will be trained via short video clips, and possible questions will be answered. For those receiving a fixed-diet plan, the specified “measuring cups” for each food group and the supplementary information in the booklets will be completely explained.

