### Statistical analysis

Statistical analyses of all data will be performed using STATA version 12.0 (Stata Corp LP, College Station, TX). The intention-to-treat approach will be used for data analysis in order to handle non-adherence. Data will be expressed as mean (SD). The one-sample Kolmogorov–Smirnov test will be used to verify the normality. If a variable distribution is not normal, the log transformation will be applied. An analysis of variance (ANOVA)/analysis of covariance (ANCOVA) model will be used to compare the values among the four intervention groups. Analysis of variance (ANOVA) and post hoc Bonferroni correction will be used for multiple comparison adjustment. Since we have 4 intervention groups (1, modified-Paleo diet with calorie counting; 2, modified-Paleo diet with a fixed diet plan; 3, medium-carbohydrate diet with calorie counting; and 4 medium-carbohydrate diet with a fixed diet plan), we will have six possible pairwise comparisons across the groups (1 with 2, 1 with 3, 1 with 4, 2 with 3, 2 with 4, 3 with 4). By these primary comparisons, we will be able to compare the effects of diets (low vs moderate carbohydrate) and delivery modes (calorie counting vs fixed diet plan) on primary outcomes. Further, there are two modules, by which confidence intervals can also be adjusted along with *p*-value for multiple comparisons. “Pwmean” and “pwcompare” modules allow for performing all pairwise comparisons using Tukey, Bonferroni, or Dunnett. An analysis of covariance (ANCOVA) will be applied to adjust the effects of confounding and baseline variables. *p* < 0.05 (two-sided) will be considered as statistically significant. Besides the null hypothesis significance testing (NHST), appropriate effect size and its 95% confidence interval will also be analyzed to provide more reasonable justification about results. Cohen’s *d* effect size, measured as the mean difference in change divided by the pooled standard deviation of the change, will be reported along with its 95% CI. Cohen’s *d* is defined as standardized mean difference (SMD) and is classified as small (*d* = 0.2), medium (*d* = 0.5), or large (*d* = 0.8) [27]. Multiple imputation will be used to correct missing data. The SAMPL guideline will be used for statistical analysis in this study [28].

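### Success on any one of three primary endpoints has no error control across endpoints and no named experimental arm, so its false-success rate is neither fixed nor held at the stated level

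*Protocol article*

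**What the plan says.** Under Study outcomes the protocol article lists the primary outcomes: "Weight, body composition, and CTRP6 (as an inflammatory marker) are the main primary outcomes in the current study". It then defines the endpoints as differences in change over ten weeks "in body composition component (weight and body fat mass) and CTRP6 concentration between the intervention groups". The decision rule follows: "Study success will be declared if either one of the primary endpoints will be statistically significant in favor of the experimental treatment".

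Under Statistical analysis the significance threshold is a p value below "0.05 (two-sided) will be considered as statistically significant". On multiplicity the section says: "Analysis of variance (ANOVA) and post hoc Bonferroni correction will be used for multiple comparison adjustment". It gives the scope of that correction by counting arms: "we will have six possible pairwise comparisons across the groups". It calls these pairs the primary comparisons and expects them to answer both the diet and the delivery-mode question. Tukey and Dunnett are mentioned as alternatives, again for pairs of arms.

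Under Intervention: "The participants will be randomly allocated to one of the four aforementioned groups". All four are active diet arms, and none is labelled experimental, control or comparator anywhere in the article. The Sample size section uses the full alpha of 0.05 for body weight alone.

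**The concern.** An at-least-one rule over three endpoints gives chance three openings. A Bonferroni correction over pairs of arms limits the error within each endpoint but does nothing between endpoints. The significance level in the article therefore does not describe the error rate of the claim the article intends to make, that the trial succeeded.

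The second gap makes the first hard to size. The rule requires a result favouring the experimental treatment, but no arm or diet has that label. Neither the deciding contrast nor its direction is fixed. A reader of the results could count any significant pair, including a pair that shares a diet and differs only in delivery mode. What is at stake is a chance difference on one endpoint being reported as success of the trial.

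**Working it through.** **Inputs from the protocol article.** Three primary endpoints with an at-least-one rule (Study outcomes). Two-sided 0.05 and Bonferroni over six pairs (Statistical analysis). Four arms; 15 per arm needed and 20 per arm enrolled; f = 0.39; power 0.80; correlation of 0.6 between the two sessions; 11 kg difference and SD 15 (Sample size).

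**Assumed.** The article gives no correlation between endpoints. The range used is weight with fat mass 0 to 0.9, and CTRP6 with each of them 0 to 0.3.

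**The plan's own figure.** The article states no overall error rate, so the sample size is the figure to reproduce. For the between-groups F test with two sessions, λ = f²·N·2/(1 + 0.6) with 3 and N − 4 degrees of freedom. At f = 0.39 and alpha 0.05 this needs N = 62, and N = 60 gives power 78.9%. The stated 60 is reproduced to within two patients, using an undivided alpha for one endpoint.

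**Error rate by formula, independent endpoints.**
- Each endpoint tested once at two-sided 0.05: 1 − 0.95³ = 14.3%.
- Six-pair Bonferroni within each endpoint, where the correction is conservative and one endpoint alone has about 4%: 1 − 0.96³ = 11.5%.
- One favourable-direction contrast per endpoint: 1 − 0.975³ = 7.3%.

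**Error rate by simulation.** Global null, four arms of 15, normal data, 100,000 trials per setting:

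| What counts as success | One endpoint | Independent | Weight-fat 0.8, CTRP6 0.3 | Weight-fat 0.9, CTRP6 0.3 |
|---|---|---|---|---|
| Any of six pairs, Bonferroni, either direction | 4.0% | 11.5% | 10.2% | 9.6% |
| Overall F test at 0.05 | 5.0% | 14.1% | 12.5% | 11.6% |
| Cross-diet pairs favouring modified-Paleo, six-pair Bonferroni | 1.5% | 4.4% | 3.8% | 3.6% |
| Diet main effect favouring modified-Paleo, two-sided 0.05 | 2.5% | 7.2% | 6.0% | 5.8% |

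Runs with 20 per arm agree within simulation error. Across all runs the ranges are about 9-12%, 11.5-14.5%, 3.5-4.6% and 5.7-7.4%, in row order.

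**Effect of a split across endpoints.** With each endpoint held at 0.05/3 = 0.0167, the total cannot exceed 3 × 0.0167 = 5% whatever the correlation. For independent endpoints it is 1 − (1 − 0.0167)³ = 4.9%.

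**Cost in power.** If 11/15 = 0.733 is read as a standardised diet main effect (the article does not say that it is), a two-sample t test gives:

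| Analysed | Alpha 0.05 | Alpha 0.0167 |
|---|---|---|
| 80 (40 v 40) | 0.90 | 0.80 |
| 60 (30 v 30) | 0.80 | 0.65 |

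On the plan's own F test at f = 0.39 and alpha 0.0167, 80% power needs 80 completers. With 60 completers power is 63%.

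**The case against.** **The rule is directional.** A reader might infer that the trial's error rate is simply 10-14% instead of 5%. The article does not support that as a flat statement. The rule asks for a favourable result, and a count of every pair in either direction ignores this. If modified-Paleo is experimental and the six-pair Bonferroni is kept, the three-endpoint rate stays below 5%. This stands as a limit on the size. It does not remove the point. The article does not fix that reading, and within it the three endpoints still raise the rate two- to threefold over one endpoint (1.5% to about 3.6-4.4% for pairs, 2.5% to about 5.8-7.2% for the main effect).

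**The 14% end is extreme.** It needs independent endpoints, although weight and fat mass are probably strongly correlated. It also needs an overall F test, which has no direction, or tests without the planned correction. This stands.

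**There may be only two endpoints.** The wording groups weight and fat mass as one component. Two independent tests at 0.05 would still give 1 − 0.95² = 9.75%, and with the pairwise Bonferroni 1 − 0.96² = 7.8%. But the article also lists weight and body composition as separate outcomes.

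**It belongs in the analysis plan.** Allocation of alpha often does. Here, however, the article itself states the success rule, the threshold and the scope of the correction, and these do not fit together.

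**The diet main effect need not be the deciding contrast.** A reader might infer that it must be, and that delivery-mode results must be barred from success. The article does not support that. The six pairs are its stated primary comparisons and delivery mode is a stated objective. Changing either is a design choice for the sponsor.

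**Conclusion.** The point holds. The success rule has no control across its three endpoints, and its key term is undefined. If any significant pair counts under the planned Bonferroni, the false-success rate is about 9-12%, where one endpoint gives about 4%. If modified-Paleo is experimental and only favourable results count, it is about 3.5-4.6% for cross-diet pairs or 5.7-7.4% for the diet main effect, against a favourable-direction share of 2.5%. Under every reading the rate is two to three times that of a single endpoint. Whether it exceeds 5% depends on a term the article leaves open. These figures assume normal data, the global null and the correlation range given above.

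**What to change.** 1. Add a rule across endpoints. For each primary endpoint, take the p value after the within-endpoint adjustment, then apply Holm (0.05/3 = 0.0167 at the first step) or Bonferroni across the three. The six pairwise comparisons can stay. A single pair then has to reach 0.05/18 = 0.0028 at the first step.
2. Have the sponsor state which arm or diet is the experimental treatment, which contrast or set of contrasts decides success, and in which direction. A single diet main effect per endpoint is one option and would need no pairwise adjustment. It would, however, replace the stated primary comparisons, and is the sponsor's choice.
3. Restate the power. The planned 0.80 rests on an undivided 0.05 for weight. Under the main-effect assumption it becomes 0.80 with 80 analysed and 0.65 with 60. A pairwise decision would have less power for a difference of the same size, because each pair uses half the patients.

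The first two changes are text, best made before outcomes are compared by arm. The real cost is the lower power per endpoint. The Trial status section expected recruitment to end in January 2021, so adding patients may not be possible. In that case the article should report the lower power.
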